| Cotinine & Urine drug screening        | •          |                          |                        |                        |                        |                        |                                            |                        |
| Neurological examination  | •          |                          | •                      |                        |                        | •                      | ①                                          | •                      |

1 Post Study Visit: On 12~19d from the phase 2 drug administration, subjects make post study visit.

2 Admission: The admission date of each phase is separated by at least 14 days.

3 Randomization: On phase1 -1d, randomization is performed and a randomization number is assigned.

4 Out-patient Visit: Subjects make outpatient visit to the Clinical Trials Center of Seoul National University Hospital on phase 1/2 5d, 6d, 7d and post-study visit to perform the scheduled procedures.

5 IP Administration: The assigned investigational drug is orally administered with 150mL of water after fasting (phase1 1d) or high-fat meal (phase2 1d) around 9 am. Set the phase1 1d administration time to 1d 0h and apply it to the subsequent study schedule.

6 Vital signs: Blood pressure, heart rate, and body temperature are measured on screening, phase 1/2 1d pre-dose(0h), 1, 2, 4, 8, 12h post-dose, 2d 0h, 3d 0h, 4d 0h, 5d 0h, 6d 0h, 7d 0h and post-study visit.

7 Physical examination: Physical examination is performed on screening, phase 1/2 1d pre-dose(0h), 2d 0h, 3d 0h, 4d 0h, 5d 0h, 7d 0h and post-study visit.

8 12-lead ECG: 12-lead ECG is measured on screening, phase 1/2 1d pre-dose(0h), 1, 2, 4, 8, 12h post-dose, 2d 0h, 3d 0h, 4d 0h, 5d 0h, 7d 0h and post-study visit.

9 Pregnancy test: For all women of childbearing potential except surgical infertility, urine hCG test is performed, and it is measured before screening, phase1 -1d before randomization, phase2 -1d and at PSV.

10 Clinical laboratory test: Hematology, blood chemistry, coagulation and urinalysis are performed on screening, phase 1/2 1d pre-dose(0h), 2d 0h, 3d 0h, 4d 0h, 5d 0h, 7d 0h and post-study visit. Serology tests are performed only on screening.

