### 9.3. Withdrawal Criteria

'Enrollment' means that the subject who participated in the study (ie, signed the informed consent form) met the inclusion/exclusion criteria and was assigned a subject randomization number according to randomization. 'Dropout' means that an enrolled subject does not complete the study. Dropout could be decided at any time during the study period for the following reasons. Dropouts of enrolled subjects from the study should be reported on the eCRF with the date of the dropout, date of the last study drug administration and the reason for the dropout.

- 1) When it is judged that it is difficult for the subject to participate in a clinical study any longer due to a clinically unacceptable serious adverse event or abnormality such as a clinical laboratory test value
- 2) When the subject takes any medication that is expected to influence the safety and pharmacokinetic characteristics of investigational drug without the permission of the investigator
- 3) When the major protocol deviation significant enough to consider discontinuation of the study is identified during the study, such as the subject was found not to be eligible based on inclusion/exclusion criteria after enrollment.

- 4) When the subject does not wish to proceed with investigational drug administration or withdraws consent during the study period
- 5) When the subject does not visit on time and cannot be contacted
- 6) In the cases where the principal investigator or sub-investigator decides to withdraw the subject from the clinical study for other reasons

Those who drop out after administering the investigational drug visit the clinical study institution within 7 days if possible of the dropout (or the first recognition of dropout) and conduct an equivalent post-study visit. However, if the subject refuses to visit, if possible, concomitant medications and lists related to adverse events should be checked by phone. Also, if the dropped out subject has clinically significant abnormal test results, follow-up should be continued. Subjects who have been dropped out due to adverse events or deviations of safety standards should be followed up until symptoms subside and abnormal laboratory test values return to standard values, or there is a satisfactory explanation for the observed changes. If follow-up is not possible, it is considered as 'failed to follow up'.

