## 10. Study Plan

### 10.1. Overall Design and Plan of the Study

This clinical study was designed as a dose blocked-randomized, double-blind, placebo-controlled, single and multiple dosing, dose-escalation phase I clinical trial.

- 1) Single ascending dose study (30 mg, 60 mg, 240 mg, 480 mg, 960 mg)

[figure not shown]

Volunteers for this study are selected as subjects if they are judged eligible for this study by undergoing screening procedures such as history taking, physical examinations, and clinical laboratory tests within 4 weeks (-28 ~ -2d) before the first administration.

Subjects are randomized after admission to the Clinical Trials Center, Seoul National University Hospital in the afternoon of the day of admission (-1d), and have dinner around 6 PM. On the dosing day (1d), the investigational drug is orally administered with 150mL of water at around 9 AM (reference time, 1d 0h), and food including drinking water is prohibited from 1 hour before administration to 4 hours after administration. Thereafter, the subjects conduct the study according to the predefined schedule and discharge at 4d. After discharge, subjects visit the Clinical Trials Center on the morning of 5d, 6d, and 7d to perform the scheduled procedures.

The subjects who complete whole study conduct the Post Study Visit(PSV) between 12d and 16d at their convenience.

- 2) Single dose study (120 mg, Food effect study)

[figure not shown]

Volunteers for this study are selected as subjects if they are judged eligible for this study by undergoing screening procedures such as history taking, physical examinations, and laboratory tests within 4 weeks (-28 ~ -2d) before the first administration.

Subjects are randomized after admission to the Clinical Trials Center, Seoul National University Hospital in the afternoon of the day of admission (phase 1 -1d), and have dinner around 6 PM. On the dosing day of the first period (phase1 1d), the investigational drug is orally administered with 150mL of water at around 9 AM (reference time, phase 1d 0h), and food including drinking water is prohibited from 1 hour before administration to 4 hours after administration. Thereafter, the subjects conduct the study according to the predefined schedule and discharge at 4d. After discharge, subjects visit the Clinical Trials Center on the morning of 5d, 6d, and 7d to perform the scheduled procedures.

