The 2nd dosing is planned with an at least 14 days after 1st dosing. The subject is admitted to the Clinical Trials Center, Seoul National University Hospital in the afternoon of the 2nd period admission day (phase 2 1d) and has dinner around 6 PM. On the dosing day of the second period (phase 2 1d), subjects start a high-fat meal (more than 900 kcal, more than 35% fat) 30 minutes before administration of the investigational drug and complete it within 20 minutes, and the investigational drugs are orally administered with 150mL of water at around 9 AM (reference time, phase1 1d 0h). Food including drinking water is prohibited from 1 hour before administration to 4 hours after administration. Thereafter, the subjects conduct the study according to the predefined schedule and discharge at 4d. After discharge, subjects visit the Clinical Trials Center on the morning of 5d, 6d, and 7d to perform the scheduled procedures.

The subjects who complete the whole study conduct the Post Study Visit(PSV) between 12d and 19d from the phase2 dosing date at their convenience.

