### 3) Multiple ascending dose study (60mg, 120 mg, 240 mg, 480 mg, 120 mg(elderly))

[figure not shown]

Volunteers for this study are selected as subjects if they are judged eligible for this study by undergoing screening procedures such as history taking, physical examinations, and clinical laboratory tests within 4 weeks (-28 ~ -2d) before the first administration.

Subjects are randomized after admission to the Clinical Trials Center, Seoul National University Hospital in the afternoon of the day of admission (-1d), and have dinner around 6 PM. On the dosing day (1d), the investigational drug is orally administered with 150mL of water at around 9 AM (reference time, 1d 0h), and food including drinking water is prohibited from 1 hour before administration to 4 hours after administration. (For the elderly, drinking water is prohibited for up to 2 hours and food intake is prohibited for up to 4 hours after administration.) Thereafter, the subjects conduct the study according to the predefined schedule and the administration of the investigational drug is continued in the hospitalized state for the repeated administration period (7 days). Subjects should maintain a fasting state for at least 10 hours before administration, and food including drinking water is prohibited from 1hour before administration. On 1d and 7d, drinking water and meals are prohibited until 4 hours after the end of administration (For the elderly, drinking water is prohibited for up to 2 hours and food intake is prohibited for up to 4 hours after administration.), and on the other administration days except for 1d and 7d, food including drinking water is prohibited until 2 hours after the end of administration. On 2d, 3d, 4d, 5d, and 6d, pharmacokinetic blood sampling is performed before administration to confirm that steady state is reached. On the morning of 7d, after oral administration of the investigational drug once, examination and evaluation are performed according to the planned schedule and then discharged on 10d. After discharge, subjects visit the Clinical Trials Center on the morning of 11d, 12d, and 13d to perform the scheduled procedures.

The subjects who complete whole study conduct the Post Study Visit(PSV) between 18d and 22d at their convenience.

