### 10.7.3. Post-Study Visit

Subjects who have completed all clinical study visit the clinical trials center and conduct the following observations and tests. Those who drop out after administering the investigational drug visit the clinical trials center within 7 days of the dropout (or the first recognition of dropout) and conduct a planned safety test at the time of post-study visit. However, if the subject refuses to visit, if possible, concomitant medications and lists related to adverse events should be checked by phone.

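### The dropout safety visit is timed from dropout and not from the last dose, so a subject who leaves during post-dose confinement can be last seen 0–10 days after dosing, while completers are seen no earlier than day 11

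*Protocol*

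**What the plan says.** **Dropouts.** Section 9.3 has subjects who drop out after dosing "visit the clinical study institution within 7 days if possible of the dropout (or the first recognition of dropout"), for the equivalent of a post-study visit. Section 10.7.3 repeats the timing without the softening words: "within 7 days of the dropout (or the first recognition of dropout) and conduct a planned safety test". If the subject refuses to come, adverse events and medication are checked by telephone where possible. That call is not tied to the last dose either.

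**Completers, single dose (10.1).** Subjects are dosed on 1d, then "the subjects conduct the study according to the predefined schedule and discharge at 4d". They have outpatient visits on 5d, 6d and 7d, and "conduct the Post Study Visit(PSV) between 12d and 16d at their convenience".

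**Completers, food effect (10.1 and the flow chart).** The post-study visit is "between 12d and 19d from the phase2 dosing date at their convenience". On spacing, the flow chart states: "The admission date of each phase is separated by at least 14 days".

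**Completers, multiple dose (10.1).** The last dose is on 7d, after which "examination and evaluation are performed according to the planned schedule and then discharged on 10d". Outpatient visits follow on 11d, 12d and 13d, and subjects "conduct the Post Study Visit(PSV) between 18d and 22d at their convenience".

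**Existing safety nets.** Section 9.3 continues follow-up of dropouts who left because of adverse events or safety deviations, or who have clinically significant test results. Section 13.5 follows known adverse events to resolution or explanation. Section 13.3 requires a serious event to be reported once the investigator learns of it. Section 17.4 brings in a subject who wants treatment for an adverse event.

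**The concern.** For completers, the post-study window fixes a minimum observation time after the last dose. For dropouts, the only clock starts at dropout or its recognition, so the sooner a subject leaves after dosing, the sooner the last planned contact can fall.

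That subject stays in the analysis. Section 14.1 puts everyone who has been dosed in the safety population, and section 12.1.2 tabulates subjects with adverse events, and event counts, by dose and treatment group. A person with shorter ascertainment is then counted beside completers in groups of 6 active and 2 placebo subjects.

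Medication enquiry has the same gap. Section 10.4.4 bars antidepressants until 2 weeks after the last dose. A dropout last seen on day 3 has 14 − 3 = 11 days of that restriction left with no planned question about it.

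**Working it through.** **Completers: days after last dose = visit day − last-dose day**

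- Single dose: 12 − 1 = 11 to 16 − 1 = 15.
- Multiple dose: 18 − 7 = 11 to 22 − 7 = 15.
- Food effect: 12 − 1 = 11 to 19 − 1 = 18, counting the dosing day as 1d as elsewhere in the protocol (12 to 19 if the text means elapsed days).

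Every completer is therefore seen at day 11 or later.

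**Dropouts**

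Let R be the day of dropout or its recognition and L the day of the last dose. The planned contact falls between R − L and R − L + 7.

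| Situation | R − L (days) | Last planned contact (days after last dose) |
|---|---|---|
| Confined after a single dose, either food-effect period included (1d to 4d) | 0 to 3 | 0 to 3 + 7 = 10 |
| Confined after the seventh dose (7d to 10d) | 0 to 3 | 0 to 3 + 7 = 10 |
| Leaving mid-dosing, multiple dose (daily doses) | 0 to 1 | 0 to 1 + 7 = 8 |
| Recognised at an outpatient visit (5d–7d or 11d–13d) | 4 to 6 | 4 to 6 + 7 = 13 |
| Food-effect subject who fails to return for period 2 | at least 14 − 1 = 13 | 13 or later |

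The first three rows always lie below 11. The shortfall runs from 11 − 10 = 1 day (11 − 8 = 3 mid-dosing) up to 11 days at the literal extreme. The fourth row overlaps the completers' window, with a shortfall of 0 to 11 − 4 = 7 days. The last row has no shortfall.

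**Drug level at the last contact**

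Section 5.2.2 predicts a human half-life of about 36 h. With mono-exponential decline, the fraction remaining after d days is 2^(−24d/36).

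- Day 3: 2^(−2) = 25%
- Day 7: 2^(−4.67) = 3.9%
- Day 10: 2^(−6.67) = 1.0%
- Day 11: 2^(−7.33) = 0.6%

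The 36 h is an allometric prediction. If the true half-life were 72 h (an assumption, for sensitivity only), the fractions would be 50%, 20%, 9.9% and 7.9% on the same days.

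**Weight of one subject**

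One such dropout is 1/6 = 17% of an active group. Section 9.4 allows replacement of subjects who leave for reasons other than adverse events, and the dropout remains in the safety population. With a replacement the share is 1/7 = 14%.

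**The case against.** The strongest reply is that the plan is consistent and its choice is sensible. Sections 9.3 and 10.7.3 agree, a prompt visit catches people before contact is lost, and no text promises dropouts the completers' window. Subjects with a known problem are already followed (9.3, 13.5), those who want treatment come back (17.4), and the safety tables are descriptive in a study that tests no hypothesis. All of this stands, and it limits the size of the point. It does not close the gap, because each of these routes needs a finding already known or a subject who comes forward. No planned contact asks a dropout who was well at an early visit what happened afterwards.

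Some stronger readings are tempting, but the documents do not support them:

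- **A reader might infer that any promptly recognised dropout is last seen at 0–10 days.** That range belongs to post-dose confinement. At the outpatient visits it is 4–13 days, and a food-effect subject who misses period 2 has no gap.
- **A reader might take the day-0 end literally, with all the drug still on board.** The wording speaks of a visit, which reads most naturally as a return after leaving. A full level at the moment of dosing also ignores absorption, since section 5.2.2 expects the peak at about 2 h. Day 0 is what the rule permits, not what is likely.
- **A reader might infer that escalation decisions rest on incomplete data.** Section 10.5 uses safety data only up to the last pharmacokinetic sampling day, so the post-study window plays no part.
- **A reader might infer that adverse events will be under-counted.** The protocol gives no dropout rate and nothing shows that late events would occur.

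**Conclusion.** The point holds in a limited form and is minor. The dropout visit replaces the post-study visit but has no minimum time from the last dose. A subject who leaves during post-dose confinement therefore gets a last planned contact 0–10 days after dosing (0–8 mid-dosing in the multiple-dose part), always short of the completers' earliest day 11.

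What goes unasked is confined to new adverse events or medications after an early visit, in dropouts who can be reached and have no known adverse event or clinically significant result. The exposure argument is real for a visit in the first few days and weak by days 7–10 at the predicted half-life. It would be stronger only if elimination proved slower than predicted.

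The conclusion assumes that 1d is the dosing day throughout and that the visit takes place within the 7 days, which section 9.3 requires only if possible. The number of subjects affected is unknown and probably small.

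**What to change.** Keep the early visit and add one sentence to sections 9.3 and 10.7.3:

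> Post-dose dropouts who agree are also telephoned about adverse events and concomitant medication in their cohort's PSV window counted from their own last dose (11–15 days; 11–18 days in the food-effect cohort), unless the dropout visit already falls in or after that window.

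Section 9.3 already has the date of the last dose recorded on the eCRF, so the anchor is available. The cost is one call per such dropout, with no extra visit, test or staff. Some subjects will decline, particularly those who have withdrawn consent, so the benefit is partial. The change is a small amendment that needs IRB approval and, if necessary, the regulator's approval (17.6).

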#### **9.4. Replacement of Study Subjects**

In this clinical study, a small number of candidate subjects can be registered in advance in consideration of the dropout rate prior to the first administration, and when dropout occurs before the first administration, the candidate subject can be replaced with the formal subject.

As this clinical study is conducted for exploratory purposes, not hypothesis testing, there is no need to replace subjects even if they drop out. In order to maintain the ratio of subjects receiving the test drug to subjects receiving placebo by dose group, additional subjects may be registered to replace subjects who dropped out. However, in the case of a subject who dropped out due to an adverse event that occurred after administration of the investigational drug, the subject is not replaced.

In the case of replacing a subject who dropped out due to reasons other than adverse events (eg, withdrawal of consent, etc.), replaced subjects are selected in the order that they passed the screening test, and the subject number that has already been used cannot be used. In the case of subject replacement, the subject number of the subject to be replaced shall be marked so that it can be recognized that it is the replaced subject, including the last digit of the number of the subject who dropped out.

## 10. Study Plan

### 10.1. Overall Design and Plan of the Study

This clinical study was designed as a dose blocked-randomized, double-blind, placebo-controlled, single and multiple dosing, dose-escalation phase I clinical trial.

- 1) Single ascending dose study (30 mg, 60 mg, 240 mg, 480 mg, 960 mg)

[figure not shown]

Volunteers for this study are selected as subjects if they are judged eligible for this study by undergoing screening procedures such as history taking, physical examinations, and clinical laboratory tests within 4 weeks (-28 ~ -2d) before the first administration.

Subjects are randomized after admission to the Clinical Trials Center, Seoul National University Hospital in the afternoon of the day of admission (-1d), and have dinner around 6 PM. On the dosing day (1d), the investigational drug is orally administered with 150mL of water at around 9 AM (reference time, 1d 0h), and food including drinking water is prohibited from 1 hour before administration to 4 hours after administration. Thereafter, the subjects conduct the study according to the predefined schedule and discharge at 4d. After discharge, subjects visit the Clinical Trials Center on the morning of 5d, 6d, and 7d to perform the scheduled procedures.

The subjects who complete whole study conduct the Post Study Visit(PSV) between 12d and 16d at their convenience.

- 2) Single dose study (120 mg, Food effect study)

[figure not shown]

Volunteers for this study are selected as subjects if they are judged eligible for this study by undergoing screening procedures such as history taking, physical examinations, and laboratory tests within 4 weeks (-28 ~ -2d) before the first administration.

Subjects are randomized after admission to the Clinical Trials Center, Seoul National University Hospital in the afternoon of the day of admission (phase 1 -1d), and have dinner around 6 PM. On the dosing day of the first period (phase1 1d), the investigational drug is orally administered with 150mL of water at around 9 AM (reference time, phase 1d 0h), and food including drinking water is prohibited from 1 hour before administration to 4 hours after administration. Thereafter, the subjects conduct the study according to the predefined schedule and discharge at 4d. After discharge, subjects visit the Clinical Trials Center on the morning of 5d, 6d, and 7d to perform the scheduled procedures.

The 2nd dosing is planned with an at least 14 days after 1st dosing. The subject is admitted to the Clinical Trials Center, Seoul National University Hospital in the afternoon of the 2nd period admission day (phase 2 1d) and has dinner around 6 PM. On the dosing day of the second period (phase 2 1d), subjects start a high-fat meal (more than 900 kcal, more than 35% fat) 30 minutes before administration of the investigational drug and complete it within 20 minutes, and the investigational drugs are orally administered with 150mL of water at around 9 AM (reference time, phase1 1d 0h). Food including drinking water is prohibited from 1 hour before administration to 4 hours after administration. Thereafter, the subjects conduct the study according to the predefined schedule and discharge at 4d. After discharge, subjects visit the Clinical Trials Center on the morning of 5d, 6d, and 7d to perform the scheduled procedures.

The subjects who complete the whole study conduct the Post Study Visit(PSV) between 12d and 19d from the phase2 dosing date at their convenience.

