## 10.7. Observations & Assessments

### 10.7.1. Screening test

The screening tests to review the eligibility of the subjects who voluntarily provided a written consent to participate in the clinical study will be performed within 4 weeks from the first administration, and subjects who have clinically significant abnormalities in the following tests will be excluded. Prior to the screening visit, perform the test after fasting for at least 8 hours. (However, if the screening test results are clinically significant, retesting can be carried out up to two times at the discretion of the investigator.)

In order to smoothly conduct clinical study, some subjects may participate as candidate subjects. Candidate subjects will be hospitalized on the same day as the formal subjects assigned with randomization numbers, and if there is a vacancy in the formal subject while participating as a candidate subject (e.g., no show of a formal subject or withdrawal of consent, etc.), the candidate subject may participate in the clinical study as a substitute for a formal subject. If there is no vacancy and the treatment group is terminated, the candidate subject may participate as a formal subject in the other treatment group with the next available schedule.

- 1) Explanation of consent form and obtaining written consent
- 2) Inclusion and exclusion criteria evaluation
- 3) Investigation of demographic data and measurement of height and weight
  - ① At the time of screening, demographic information such as gender and age of the test subject is checked, and drinking and smoking history are asked.
  - ② Measurement of height and weight
    - Height: To 1 decimal place, cm
    - Weight: Rounded from 2 decimal places to 1 decimal place, kg
    - Body mass index: Rounded from 2 decimal places to 1 decimal place, kg/m^2
- 4) Investigation of drug administration history and medical history

Investigate recent medical history, including past medical history within 3 years, and drug administration

history within 5 weeks.

5) Physical examination

Physical examination includes examination of general condition, nutritional status, skin/mucous membranes, eyes (except for visual loss), otolaryngology, thyroid, lung/respiratory system, heart/circulatory system, abdomen, kidney/urogenital system, nerve/psychiatric system, spine/limb/tumors, peripheral circulation, lymphatic system, and other organs.

6) Vital signs

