## 2) Vital sign

Blood pressure, pulse rate, and body temperature(tympanic) are measured on phase 1/2 1d pre-dose(0h), 1, 2, 4, 8, 12h post-dose, 2d 0h, 3d 0h, 4d 0h, 5d 0h, 6d 0h, and 7d 0h.

| Scheduled time point                 | Time window |
|--------------------------------------|-------------|
| phase 1/2 1d 0h, 2d 0h, 3d 0h, 4d 0h | -60 min     |
| phase 1/2 1d 1, 2, 4, 8, 12h         | ±30 min     |

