## 5) Clinical laboratory test

Clinical laboratory tests are performed on phase 1/2 1d pre-dose(0h), 2d 0h, 3d 0h, 4d 0h, 5d 0h, and 7d 0h.

| Scheduled time point                 | Time window |
|--------------------------------------|-------------|
| phase 1/2 1d 0h, 2d 0h, 3d 0h, 4d 0h | -60 min     |

Clinical laboratory tests include the following lists.

|                             |                                                                                                                                                                                                                                                    |
|-----------------------------|----------------------------------------------------------------------------------------------------------------------------------------------------------------------------------------------------------------------------------------------------|
| Hematology test      | WBC with differential count (segmented neutrophil, eosinophil, basophil, lymphocyte, monocyte), RBC, hemoglobin, hematocrit, platelet                                                                                                              |
| Blood chemistry test | AST, ALT, ALP, $\gamma$ -GTP, LDH, CPK, glucose, total cholesterol, triglyceride, creatinine, BUN, uric acid, total bilirubin, total protein, albumin, sodium, potassium, calcium, chloride, phosphorus, eGFR (measured using the CKD-EPI formula) |
| Coagulation test     | PT (INR), aPTT                                                                                                                                                                                                                                     |
| Urine test           | dipstick (color, pH, specific gravity, albumin, bilirubin, glucose, urobilinogen, ketone, nitrite, occult blood, WBC) microscopy (RBC, WBC, squamous cell, others)                                                                                 |

6) Neurological examination

A brief neurological examination (Appendix 2) is performed on phase 1/2 1d pre-dose(0h), 4h, 12h post-dose, 4d 0h, and 7d 0h.

| Scheduled time point   | Time window  |
|------------------------|--------------|
| phase 1/2 1d 0h, 4d 0h | -60 min      |
| phase 1/2 1d 4, 12h    | $\pm 30$ min |

8) Blood samplings and urine collections for PK analysis

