#### 12.1.2. Safety/Tolerability Analysis

All AEs are classified using the MedDRA (Medical Dictionary for Regulatory Activities). Summarize the number of subjects (occurrence rate) and the number of occurrences of adverse events/adverse drug reactions and serious adverse events/adverse drug reactions by dose group and treatment group. Vital signs, 12-lead ECGs, and clinical laboratory tests are presented as descriptive statistics (mean, standard deviation, median, minimum, maximum) for the values measured at each time point and the amount of change from the baseline by dose group for continuous variables. In addition, for test results classified as normal, not clinically significant abnormal (NCS), and clinically significant abnormal (CS), a shift table after administration compared to the baseline is presented. A separate list is presented when there is a change from a normal or a not clinically significant abnormal (NCS) to a clinically significant abnormal (CS). Neurological examination summarizes the frequency of clinically significant abnormalities at each time point, and descriptive statistics according to appropriate classification such as dose group.

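### In the fed period of the food-effect cohort, the 60-minute window for the pre-dose laboratory sample spans the high-fat meal, so pre-dose glucose and triglyceride can be fasted in some subjects and post-meal in others

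*Protocol*

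**What the plan says.** **Meal timing.** Protocol section 10.1, item 2 (food-effect study), says that on the phase 2 dosing day "subjects start a high-fat meal (more than 900 kcal, more than 35% fat) 30 minutes before administration of the investigational drug" and must "complete it within 20 minutes". Dosing is at around 9 AM.

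**Laboratory schedule.** Section 10.7.2.2, item 5: "Clinical laboratory tests are performed on phase 1/2 1d pre-dose(0h), 2d 0h, 3d 0h, 4d 0h, 5d 0h, and 7d 0h". The window table below it has a single row for both periods: "phase 1/2 1d 0h, 2d 0h, 3d 0h, 4d 0h | -60 min". Glucose and triglyceride are in the chemistry panel.

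**Other pre-dose assessments.** Vital signs are "measured on phase 1/2 1d pre-dose(0h), 1, 2, 4, 8, 12h post-dose". Vital signs, ECG, physical examination and the brief neurological examination all have the same pre-dose window of 60 minutes, with no distinction between periods.

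**Fasting for tests.** The only fasting rule attached to laboratory tests is in section 10.7.1: "Prior to the screening visit, perform the test after fasting for at least 8 hours".

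**Analysis.** Section 12.1.2 summarises vital signs, ECG and laboratory tests by "the values measured at each time point and the amount of change from the baseline by dose group for continuous variables". For results classed as normal, abnormal but not clinically significant (NCS), or clinically significant (CS), it adds a shift table against baseline. It does not say which measurement is the baseline in each period.

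**The concern.** A window suited to a fasted morning has been applied unchanged to a morning with a planned meal before dosing. In phase 1 a sample drawn anywhere in the window is fasting. In phase 2 a sample at 45 minutes before dosing is fasting, and one at 5 minutes before dosing follows a meal of more than 900 kcal. Both comply with the protocol.

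Glucose and triglyceride are the items in the panel for which fasting state is the evident worry. If the phase 2 pre-dose sample is the fed-period baseline, whatever the meal adds to that value is subtracted from every later change in that subject, and in subjects sampled before the meal it is not. The changes and shifts summarised for the cohort would then refer to different starting states. This has to be settled in the protocol: an analysis plan can choose which value to call baseline, but it cannot recover a pre-meal sample that was never drawn.

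**Working it through.** The protocol gives no figure to reproduce here. The check is an overlap of intervals on the dosing clock, with 0 as the time of administration.

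**Inputs**
- Sampling window: -60 to 0 min, length 60 min (section 10.7.2.2, item 5; same row for phases 1 and 2).
- Meal start: -30 min (section 10.1, item 2).
- Latest permitted meal end: -30 + 20 = -10 min (section 10.1, item 2).

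**Share of the phase 2 window** (overlap divided by 60 min)

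| Part of window | Interval (min) | Length | Share |
|---|---|---|---|
| Before the meal | -60 to -30 | 30 min | 30/60 = 50% |
| During the permitted meal time | -30 to -10 | 20 min | 20/60 = 33% |
| After the latest meal end | -10 to 0 | 10 min | 10/60 = 17% |
| After the meal has started (sum of the last two) | -30 to 0 | 30 min | 30/60 = 50% |

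A subject who finishes early has more than 10 post-meal minutes in the window. The 50% after meal start does not change.

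**Phase 1 for comparison.** Section 10.4.1 requires at least 10 hours of fasting before dosing. At the earliest point of the window the subject has fasted at least 10 - 1 = 9 hours, so all 60 minutes are fasting.

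**Does any other text force the phase 2 sample to precede the meal?**
- Section 10.7.1 sets an 8-hour fast, for screening only.
- Section 10.1, item 2, also bans food from 1 hour before dosing in the fed period. A meal at -30 min lies inside that ban, so the two statements conflict.
- Section 10.8 requires at least 10 hours of fasting before dosing and, unlike section 10.4.1, makes no exception for the fed period. That also conflicts with the meal.
- None of these places the laboratory sample before the meal.

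**Effect of closing the window at meal start.** Window -60 to -30 min; overlap with the meal and the time after it = 0 min, against 30 min now.

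**Who is affected.** Cohort 3: 6 active + 2 placebo = 8 subjects (section 9.1), on one morning each.

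**The case against.** The strongest case on the other side accepts the timings and disputes the consequences. Most of it stands.

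- **No fed-versus-fasted safety comparison is planned.** A reader might infer that the window biases such a comparison. Section 12.1.2 summarises by dose and treatment group, and section 14.2 compares safety findings only where necessary. The only planned food-effect evaluation is the geometric mean ratio of Cmax and AUC, which uses none of these baselines.
- **The baseline is not defined per period.** The analysis plan, not shown, may define it, so its absence is no finding. The consequence for change scores is therefore conditional. But section 12.1.2 also summarises the measured values at each time point, so the phase 2 pre-dose row can be mixed whatever the baseline is.
- **The direction of bias is not established.** A reader might expect next-morning values to show an artificial fall. That needs the later samples to be fasting, and no fasting rule is stated for the samples from day 2 to day 7.
- **Masking of a later abnormality is limited.** A separate list is triggered by a move from normal or NCS to CS. A meal-related value judged NCS would not hide a later CS value; only a baseline already judged CS would.
- **Vital signs and ECG are a different case.** The early post-dose readings follow the same meal. A pre-meal baseline would put the meal effect inside the apparent post-dose change, so requiring one is debatable.
- **No meal effect is argued for the physical or neurological examination.**
- **The 50% is a share of permitted minutes, not of samples.** A site that draws every sample before the meal complies fully. Placebo subjects have the same meal and window, so neither arm is systematically favoured.

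What the objection does not remove is that the protocol leaves the fasting state of the phase 2 pre-dose laboratory sample to chance.

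**Conclusion.** The point holds for the laboratory sample, as a minor improvement. Half of the permitted phase 2 pre-dose window (30 of 60 minutes) falls during or after the high-fat meal, so pre-dose glucose and triglyceride can be collected in different fasting states within one cohort. If phase 2 day 1 pre-dose serves as the fed-period baseline, which is the natural reading but is not stated, the change-from-baseline and shift summaries of these tests are inconsistent across subjects.

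The documents do not give the size of the meal effect, and a sample in the window is drawn at most 30 minutes after the meal begins. The consequence is confined to descriptive safety summaries of 8 subjects. The pharmacokinetic food-effect result is not affected.

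**What to change.** - **Laboratory tests (section 10.7.2.2, item 5).** Split the window row. Keep 60 minutes before dosing for phase 1 day 1, and for days 2 to 4 of both phases. For phase 2 day 1, require the sample before the high-fat meal starts, that is between -60 and -30 min. If 30 minutes is too short, let the window open earlier.
- **Vital signs and ECG (items 2 and 3).** Require only that the phase 2 pre-dose reading be taken at one consistent point relative to the meal in all subjects.
- **Physical and neurological examinations.** No change.
- **Food restrictions.** Reconcile the one-hour pre-dose food ban in section 10.1, item 2, and the 10-hour fast in section 10.8 with the planned fed-period meal.

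The cost is a few edited table rows and slightly earlier procedures on one morning for 8 subjects. No test is added.
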